#### Cost-utility analysis

In the cost-utility analysis, the effectiveness will be measured by using the QALYs (which considers both the quantity and quality of life). The health state utilities (which indicates the ‘Q’ in QALYs) will be firstly estimated based on the EQ-5D-5L questionnaire and scored using Australian-specific tariff. Alternatively, the health state utility generate from a cancer-specific quality of life instrument QLQ-C30 will also be considered to investigate the robustness of the results using a recently published Australian-specific tariff.[54] Resource use and total costs associated with the two management arms will be populated based on the data collected from the trial. Key resource use items will include rectal cancer treatment costs (such as surgery, imaging, chemotherapy, and endoscopy), and any associated healthcare costs. Both costs and benefits will be discounted by 5% in the base model, in line with government policy. Decision uncertainty will be summarised through the presentation of cost effectiveness acceptability curves.

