**Methods:**

Adult patients with a diagnosis of rectal cancer planned to receive neoadjuvant long course chemoradiotherapy (± subsequent combination chemotherapy) will be consented into the study prior to commencing treatment. After completing the chemoradiotherapy (± subsequent combination chemotherapy), based on the clinical response, subjects will be allocated to one of the following arms: subjects who achieved a clinical complete response will be allocated to the watch and wait arm and others to the standard management arm (which includes resection). The aim of the study is to determine the rate of local failure and other safety and efficacy outcomes in the watch and wait arm. Patient reported outcome measures and the use of biomarkers as part of the clinical monitoring will be studied in both arms of the study.

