### Assessment plan

Schedule of assessments is summarized in Table 1. Schedule of PROMs is summarized in Table 2.Timing of the monitoring visits will be calculated from the allocation visit.The watch and wait arm: monitoring visits: monitoring visits and procedures to be scheduled according to the assessment timetable (± 2 weeks)The standard management arm: PROMs questionnaires to be completed according to the to the assessment timetable (± 2 weeks)Follow-up after stopping the study: If a patient wishes to stop the study visits, they will be requested to allow their ongoing health status to be periodically reviewed via continued study visits or phone contact or from their general practitioner, or medical records, state-based cancer registries and/or the national mortality registry.For patients who have been lost to follow-up, Medicare may be used to provide updated contact information and/or hospitalisations and the national registry may be used to collect mortality information.

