#### Cost effectiveness

To determine the cost effectiveness of the watch and wait approach, a within-trial economic evaluation from a healthcare sector perspective will be conducted using a cost-utility analysis (CUA), in which the effectiveness will be measured by quality-adjusted life-years (QALYs). The cost-utility analysis involves estimating the incremental cost effectiveness ratios (ICERs) of the watch and wait approach versus standard management plan. For the within-trial economic evaluation, only costs and effects that accumulate within the trial participation up to 24 months will be considered.

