### Statistical analysis

Analyses will include all patients enrolled. Local control will be assessed by the proportion, together with the 95% confidence interval, of patients not failing locally as their first event at 2 years. This proportion will be estimated using a competing risk cumulative incidence curve where distant failure or death prior to any failure is considered as a competing risk. This will be estimated in both groups.

Time-to event endpoints of progression free, local control and overall survival will be described using the method of Kaplan–Meier or cumulative incidence. Formal comparisons between groups will be performed using logrank, Cox proportional hazards, Gray and Fine & Gray methods. Exploratory comparative analyses include univariate and multivariate regression models for time-to-event outcomes, regression models for continuous outcomes and logistic regression analyses for binary outcomes. Other exploratory analyses will also be performed as appropriate. No imputation for missing data is envisaged which will be assumed to be missing at random. Quality of life will be summarized using trajectories over the follow-up time.

In the watch and wait arm: the study will be stopped if the number of cases with local failure reaches 3 cases in the first 15 participants, and 5 cases in the first 30 participants at 3 years based on the charts of Mehta and Cain. [55] (Table 3).

Study Committees.Trial management committee

The trial management committee will oversee study planning, monitoring, progress, review of information from related research, and implementation of recommendations from other study committees and external bodies (e.g., ethics committees).Independent safety and data monitoring committee

This study has an independent safety and data monitoring committee including experts in the field who are not involved in this study.

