^b^Allocation phase includes Run-in phase (6–8 weeks after finishing CRT) and allocation visit (8–10 weeks after finishing CRT)

^2nd MRI only if CT scan and endoscopic evaluation indicate Ccr

**Table 2. Tab2:** Schedule of assessments: Patient Reported Outcome Measures

All Participants	Month	SCQ	EORTC QLQ-C30	CR29 EORTC QLQ	EQ-5D-5L	MSKCC BFI	LARS	FCRI-SF	Questions Response efficacy	CaSUN
Screening visit		X	X	X	X	X	X	X		
Chemoradiotherapy										
Run-in phase		X	X	X	X	X	X	X		
Allocation visit	0									
12-month visit	12	X	X	X	X	X*	X*	X	X	X
24-months visit	24	X	X	X	X	X*	X*	X	X	X

^a^Only if participant does not have a stoma

**Table 3. Tab3:** .

% Local failure rate	Sample size	Stop the study if the number of local failure cases is equal to or more than:
15%	15	3
15%	30	5

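### Utility is not measured between run-in and month 12, so the 24-month QALYs miss temporary losses in that interval, and the no-imputation rule leaves incomplete utilities without a method

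*Protocol article*

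**What the plan says.** The protocol article's Cost effectiveness section plans a within-trial cost-utility analysis, "estimating the incremental cost effectiveness ratios (ICERs) of the watch and wait approach versus standard management plan", and states that "only costs and effects that accumulate within the trial participation up to 24 months will be considered". Under Cost-utility analysis, the base-case utilities "will be firstly estimated based on the EQ-5D-5L questionnaire and scored using Australian-specific tariff". As a check, "the health state utility generate from a cancer-specific quality of life instrument QLQ-C30 will also be considered to investigate the robustness of the results". The same section lists surgery among the key resource items to be costed.

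The Assessment plan points to Table 2 for the timing of questionnaires. Table 2 marks EQ-5D-5L and QLQ-C30 at screening, run-in, month 12 and month 24, and leaves the allocation row (month 0) blank. Table 1 agrees: it has time points at months 3, 6 and 9 in both arms, none with patient-reported outcomes marked. In the standard arm those time points carry only outcome events, with other assessments left to standard care.

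On missing data, the Statistical analysis section says: "No imputation for missing data is envisaged which will be assumed to be missing at random". It makes no exception for the economic evaluation and names no model for utilities.

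**The concern.** Patients are allocated at month 0, and standard management includes resection. The date of surgery is not stated, but resection and early recovery would normally fall between run-in and month 12. No utility is recorded in that interval. A straight line drawn from the run-in value to the month 12 value cannot show a loss that comes and goes between them, yet the operation that caused it enters the cost side in full. The QLQ-C30 check has the same time points, so it cannot reveal the problem. No later analysis plan can recover utilities that were never collected.

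The missing-data rule adds a second weakness. A QALY computed patient by patient needs every form in the period. With no imputation and no model named, a patient with one missing form has no QALY. Missing at random does not in general justify an analysis of complete cases.

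At stake is the cost-effectiveness result, which the Discussion says should help guide health policy.

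**Working it through.** The plan states no QALY, ICER or form-completion figure, so there is nothing of its own to reproduce. The sizes below are illustrations.

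**Inputs from the documents**
- EQ-5D-5L time points: screening, run-in, month 12, month 24 (Table 2).
- Horizon: 24 months (Cost effectiveness).
- Arm sizes: 50 watch and wait, 200 standard management (Sample size).

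**Assumptions**
- Utilities are joined by straight lines, run-in is taken as month 0, and QALYs are undiscounted.
- The utility fall after surgery is 0.1 to 0.3, recovering linearly over 3 to 6 months, all before month 12.
- Each form is missing for 5% to 10% of patients, independently across time points.

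**Step 1: loss that the schedule cannot see.** For a fall of size d recovering linearly over m months, loss = d × (m/12) / 2.
- d = 0.1, m = 3: 0.1 × 0.25 / 2 = 0.0125 QALY.
- d = 0.2, m = 6: 0.2 × 0.5 / 2 = 0.050 QALY.
- d = 0.3, m = 6: 0.3 × 0.5 / 2 = 0.075 QALY.

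Widening the duration to 1.5 to 9 months gives 0.006 to 0.113.

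**Step 2: one curve worked through.** Take utility 0.80 at months 0, 12 and 24, a fall of 0.20 at month 1, and linear recovery by month 7.
- True 24-month QALY: 0.80 × 2 − 0.20 × (6/12) / 2 = 1.550.
- Planned schedule (0, 12, 24): 0.80 × 2 = 1.600, which is 0.050 too high.
- With month 6 added, the error is 0.033.
- With months 3 and 6 added, the shortfalls read are 0.133 and 0.033. The recorded loss is (0.133 × 3/2 + (0.133 + 0.033) × 3/2 + 0.033 × 6/2) / 12 = 0.046, leaving an error of 0.004.

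**Step 3: a loss that persists to month 12.** If utility falls by 0.1 at month 1 and stays down, the true first-year loss is 0.1 × 11/12 = 0.092. The straight line from run-in to month 12 records 0.1 / 2 = 0.050. Lasting losses are captured, but only in part.

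**Step 4: complete QALYs if incomplete patients are left out.** A month 0 to 24 QALY needs three forms (run-in, 12, 24), so the complete share is r³, where r is completion per form.
- r = 0.95: 0.95³ = 0.857, so 14% lack a QALY. That leaves about 43 of 50 in watch and wait and 171 of 200 in the standard arm.
- r = 0.90: 0.90³ = 0.729, so 27% lack a QALY. That leaves about 36 of 50 and 146 of 200.

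**The case against.** The strongest reply concerns the missing-data half. The article does not say that incomplete patients will be excluded. A likelihood-based mixed model uses partial data, needs no imputation and is valid under missing at random, and mean QALYs can be built from its fitted means. Handling of incomplete utilities is also often left to a separate plan. A reader might infer from the no-imputation sentence that a complete-case analysis is certain; the text does not support that. What stands is narrower: the sentence is a stated general rule, it makes no exception for the economic analysis, and no alternative for utilities is given.

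On direction, a reader might infer a bias against watch and wait, because the unseen surgical loss sits mainly in the comparator. The documents do not settle this. The Chemotherapy section recommends three months of adjuvant doublet chemotherapy in watch and wait for suitable patients who did not have total neoadjuvant therapy, and early salvage surgery can fall in the same interval. Both arms have unmeasured losses. It might also be supposed that relapsing patients are the likeliest to miss forms; nothing in the document says so.

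On size, the falls in utility and the missing rates are assumed. Counting the screening form as a fourth would give 1 − 0.9⁴ = 34% incomplete at 10% missing, but that applies only if QALYs start at screening, which the plan does not state. If the same patients tend to miss several forms, more patients are complete than under independence.

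Finally, cost-effectiveness is one of several secondary objectives, and Table 2 already lists nine instruments, so sparse timing may be a deliberate limit on burden. That bears on priority. It does not close the gap.

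**Conclusion.** The point holds. The schedule as written cannot measure a temporary utility loss between run-in and month 12 in either arm, while surgery is costed in full, so the ICER is distorted. The net direction is uncertain. For an assumed fall of 0.1 to 0.3 recovering linearly over 3 to 6 months, about 0.013 to 0.075 QALY per operated patient is unseen; losses still present at month 12 are partly captured. No incremental QALY is given, so the effect on the cost-effectiveness conclusion cannot be stated. This rests on surgery falling inside the interval, which is inferred from allocation at month 0.

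The missing-data part is conditional. If the stated rule leads to complete-case QALYs, 14% to 27% of patients would lack one under the assumed 5% to 10% missing per form.

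Neither co-primary endpoint is affected. The arms are also formed by response, so the ICER remains confounded whatever is done here.

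**What to change.** 1. In Tables 1 and 2, add EQ-5D-5L alone at months 3 and 6 in both arms. In the standard arm, where Table 1 marks only outcome events at those time points, collect it by phone or post.
2. In the Statistical analysis section, exempt the cost-utility analysis from the no-imputation rule. Name multiple imputation for EQ-5D-5L and costs, or a likelihood-based mixed model for utilities, with complete-case analysis as a sensitivity analysis.

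The cost is up to two five-item forms per participant (2 × 250 = 500 at most), some added contact in the standard arm, and modest analysis work.

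The added forms will not catch everything. For a fall of 0.1 at month 1 that recovers by month 4, the month 3 form reads a shortfall of 0.033 and the month 6 form none. The recorded loss is (0.033 × 3/2 + 0.033 × 3/2) / 12 = 0.008 of the true 0.0125. A loss fully over by month 3 would still be missed.

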### Safety reporting

#### Definitions

Adverse event (AE) is any untoward medical occurrence in a patient or clinical investigational subject, and which does not necessarily have a causal relationship with the management approach (MRI, endoscopy and surgery).

For this trial, only adverse events deemed related to the study procedures (MRI, endoscopy and surgery) will be collected and reported on.

A serious adverse event (SAE) is any untoward medical occurrence that:results in death,is life-threatening (i.e., the subject is at risk of death at the time of the event),requires inpatient hospitalisation or prolongation of existing hospitalisation,results in persistent or significant disability or incapacity,is a congenital anomaly/birth defectother important medical events which, in the opinion of the investigator, are likely to become serious if untreated, or as defined in the protocol.

#### Reporting of SAEs

The investigator is responsible for reporting all SAEs occurring during the study to the principal investigators within 1 working day of the investigator becoming aware of the event using the SAE form. SAEs must be reported up to 30 days from the end of study intervention. The principal investigators must notify the local Human Research Ethics Committees (HREC) as required.

#### Central review and specimen collection

Central tissue collection: paraffin-embedded tissue blocks will be collected for central histology review and for translational studies. Fresh tissue will be collected for biomarker studies.

Central blood collection: blood collection is required for all study patients. Serum and plasma for biomarkers will be collected and initially processed at each site. The frozen samples will be sent to a central lab for analysis.

Central imaging collection: Central Review: MRI scans will be reviewed centrally.

Other central collection: stool specimens will be collected and will be studied centrally to assess for gut microbiome. If there are available samples which have been collected and stored and they meet the sample requirements per the lab manual, these may be used in addition to or in place of collecting new samples.

### Statistical considerations

#### Sample size

The sample size is determined by utilizing the precision of the expected rate of local failure for patients with cCR after CRT. Based on available literature, the failure rate by 3-years is assumed to be 5%. A sample of 50 participants with cCR will be required to allow for 47 assessable participants (considering 5% potential drop out). This sample size calculation provides a precision of ± 10% with 95% confidence for the estimate of 5% local failure rate. Expecting 20% rate of cCR, this will translate into a total of 250 participants to be enrolled into the study to result in 50 participants in the watch and wait arm. (50 participants in the watch and wait arm and 200 in the standard management arm).

### Statistical analysis

Analyses will include all patients enrolled. Local control will be assessed by the proportion, together with the 95% confidence interval, of patients not failing locally as their first event at 2 years. This proportion will be estimated using a competing risk cumulative incidence curve where distant failure or death prior to any failure is considered as a competing risk. This will be estimated in both groups.

Time-to event endpoints of progression free, local control and overall survival will be described using the method of Kaplan–Meier or cumulative incidence. Formal comparisons between groups will be performed using logrank, Cox proportional hazards, Gray and Fine & Gray methods. Exploratory comparative analyses include univariate and multivariate regression models for time-to-event outcomes, regression models for continuous outcomes and logistic regression analyses for binary outcomes. Other exploratory analyses will also be performed as appropriate. No imputation for missing data is envisaged which will be assumed to be missing at random. Quality of life will be summarized using trajectories over the follow-up time.

In the watch and wait arm: the study will be stopped if the number of cases with local failure reaches 3 cases in the first 15 participants, and 5 cases in the first 30 participants at 3 years based on the charts of Mehta and Cain. [55] (Table 3).

Study Committees.Trial management committee

The trial management committee will oversee study planning, monitoring, progress, review of information from related research, and implementation of recommendations from other study committees and external bodies (e.g., ethics committees).Independent safety and data monitoring committee

This study has an independent safety and data monitoring committee including experts in the field who are not involved in this study.

Ethics and administrative issues:Ethics and regulatory complianceThis study will be conducted according to the Note for Guidance on Good Clinical Practice (CPMP/ICH/135/95) annotated with TGA comments (Therapeutic Goods Administration DSEB July 2000) and in compliance with applicable laws and regulations. The study will be performed in accordance with the NHMRC Statement on Ethical Conduct in Research Involving Humans (© Commonwealth of Australia 2007), and the NHMRC Australian Code for the Responsible Conduct of Research (©Australian Government 2007), and the principles laid down by the World Medical Assembly in the Declaration of Helsinki 2008.To this end, no patient will be recruited to the study until all the necessary approvals have been obtained and the patient has provided written informed consent. Further, the investigator shall comply with the protocol, except when a protocol deviation is required to eliminate immediate hazard to a subject. In this circumstance the principal investigator and HREC must be advised immediately.Protocol amendmentsChanges and amendments to the protocol can only be made by the trial management committee. Approval of amendments by the institutional HREC is required prior to their implementation. In some instances, an amendment may require a change to a consent form. The Investigator must receive approval/advice of the revised consent form prior to implementation of the change. In addition, changes to the data collected, if required, will be incorporated in the amendment.Confidentiality

The study will be conducted in accordance with applicable privacy acts and regulations. All data generated in this study will remain confidential. All information will be stored securely at the clinical trials unit and will only be available to people directly involved with the study and who have signed a confidentiality agreement.Data handling and record keepingAll trial data required for the monitoring and analysis of the study will be recorded on the case report forms (CRF). All required data entry fields must be completed. Data corrections will be done according to the instructions provided. The investigator will be asked to confirm the accuracy of completed CRFs by signing key CRFs as indicated. All study-related documentation will be maintained for 15 years following completion of the study.Study MonitoringData from this study will be monitored by clinical trials unit or their delegates. Monitoring will include centralised review of CRFs and other study documents for protocol compliance, data accuracy and completeness.Publication policy

The trial management committee will appoint a writing committee to draft manuscript(s) based on the trial data. Manuscript(s) will be submitted to peer-reviewed journal(s). All publications must receive prior written approval from the principal investigators prior to submission.

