## Methods

### Aims and objectives

#### Primary objectives

To determine the safety and efficacy of the watch and wait approach, by measuring the following endpoints in the watch and wait arm:Co-Primary endpoint 1: The ‘two-year local failure rate’Co-Primary endpoint 2: The rate of rectal preservation

Secondary objectives:To determine the safety of the watch and wait strategy by measuring the following endpoints (in the watch and wait arm):The ‘two-year local regrowth rate’The ‘two-year distant metastasis rate’The overall survivalThe ‘incurable disease-free survival rate’ (recurrent cancer that cannot be surgically excised with the intention of achieving a cure)Evaluate the role of biomarkersPlasma and tumour biopsy biomarkers (non-coding RNAs, methylated DNA), TILs, organoids and gut microbiome:i)To predict cCR (in both arms)ii)To identify residual disease, micrometastases and recurrence risk (in both arms)iii)As prognostic biomarkers (in both arms)Imaging biomarkers (mrTRG, diffusion and T2 signs)i)To predict sustained cCRPROMs (in both arms)Quality of life (quality of life and health related quality of life)Bowel related quality of lifeFear of cancer recurrenceSupportive care needsTo evaluate a defined monitoring schedule in the watch and wait armCost effectiveness analysis: (both arms)

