### Outcomes, endpoints and other measures

#### Safety and efficacy

Two-year local failure rate (Co-Primary Endpoint)This endpoint will be measured in the watch and wait arm only. It is defined as local recurrence (i.e., recurrence in the region of the rectum, mesorectum and adjacent lymph nodes) that cannot be resected with clear margins.Metastatic disease:Metastatic disease in the presence of local recurrence is considered ‘local failure’Metastatic disease in the absence of local cancer recurrence is not considered ‘local failure’The rate of rectal preservation (Co-Primary endpoint)This endpoint will be measured in the watch and wait arm only. It is defined as the rate of organ (rectal) preservation at two years.

Rate of incurable-disease free survival (incurable-disease or death)Defined as the interval from date of registration to the date of first evidence of ‘local failure’ or ‘distant metastatic disease’ or death, whichever occurs firstOverall survival (death from any cause)Overall survival is defined as the interval from the date of registration to date of death from any cause, or the date of last known follow-up alive.Two-year local recurrence rateLocal Recurrence is defined as evidence of recurrent disease within the pelvis, found by examination, endoscopy or imaging (CT or MRI). Biopsy and pathological confirmation are encouraged if technically possible and safe.Two-year distant recurrence rateDistant Recurrence is defined as evidence of recurrent disease other than local recurrence, found by imaging or on examination.

Translational research (biomarkers).

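### The only stated analysis of two-year local failure counts first events and treats earlier metastasis as a competing risk, while the co-primary endpoint definition has no first-event condition

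*Protocol article*

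**What the plan says.** All references are to the protocol article.

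**Endpoint.** Primary objectives lists "Co-Primary endpoint 1: The ‘two-year local failure rate" as a measure in the watch and wait arm. Under Outcomes, endpoints and other measures (Safety and efficacy), the endpoint is local recurrence "that cannot be resected with clear margins". Two rules on metastasis follow: "Metastatic disease in the presence of local recurrence is considered ‘local failure", and "Metastatic disease in the absence of local cancer recurrence is not considered ‘local failure". Neither rule sets an order of events or requires local failure to come first. The same section defines local recurrence separately, as a secondary endpoint.

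**Analysis.** Statistical analysis assesses *local control* by the proportion "of patients not failing locally as their first event at 2 years". It is read from a cumulative incidence curve in which "distant failure or death prior to any failure is considered as a competing risk". The estimate is to be made in both groups. The text does not call it the primary analysis, but gives no other analysis of local failure at two years.

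**Monitoring.** The stopping rule in the same section counts cases of local failure and does not mention first events.

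**The concern.** The definition and the analysis classify the same patient differently. Suppose a patient has metastasis at month 6 and pelvic recurrence at month 9. By the definition this is a local failure. In the analysis the patient has already left as a competing event and stays among those not failing locally. Nothing elsewhere in the article restores such a patient.

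The stake is a co-primary safety endpoint with very few expected events, so one patient's classification is visible in the result. If the stopping rule is applied with the endpoint definition, which is its natural reading, monitoring and final analysis could also report different counts for the same patients.

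A second ambiguity sits in the same sentences. The analysis speaks of failing locally and of any failure, and does not say whether a regrowth that is resected with clear margins counts as either. The definition says it is not a local failure.

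**Working it through.** **1. The plan's own figures.** From Sample size: 47 assessable, 5% drop-out, 20% clinical complete response, and "the failure rate by 3-years is assumed to be 5" per cent.
- 47 / 0.95 = 49.5, rounded up to 50; 50 / 0.20 = 250. Both agree with the article.
- At n = 47 and p = 5%, the Wilson 95% interval is 1.5% to 15.3%. Its upper arm of about 10 points matches the stated precision (the Wald half-width is 6.2 points).
- Expected events: 0.05 × 47 = 2.35, so two or three. This carries the 3-year rate over to the 2-year endpoint, which is an assumption.

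**2. Patient courses within two years, side by side.**

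| Course | Endpoint definition | Stated analysis |
|---|---|---|
| Unresectable local recurrence first | Event | Event |
| Metastasis, never local recurrence | Not an event | Competing event |
| Metastasis first, then pelvic recurrence that is unresectable or present together with the metastasis | **Event** | **Competing event; counted as not failing locally** |
| Local recurrence and metastasis found together | Event | Not settled by the wording |
| Regrowth resected with clear margins, no metastasis | Not an event | Not settled |
| Salvaged regrowth, later unresectable recurrence | Event | Not settled |
| Death without any failure | Not an event | Competing event |

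The third row is the clear contradiction. Treating death as a competing event is sound.

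**3. Size of the metastasis-first loss.** Each such patient changes the estimate by 1/47 = 2.1 points. Let D be the proportion with metastasis as first event by two years, and q the proportion of those with a qualifying local failure afterwards, still within two years. The loss is D × q. Neither value is in the documents; the ranges below are assumptions.

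| D | q | Loss, points | Patients of 47 | Analysed rate if the defined rate is 5% |
|---|---|---|---|---|
| 5% | 10% | 0.5 | 0.2 | 4.5% |
| 10% | 20% | 2.0 | 0.9 | 3.0% |
| 15% | 30% | 4.5 | 2.1 | 0.5% |

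One patient as an illustration, with exact binomial 95% intervals that ignore censoring:
- 3/47 = 6.4% (1.3% to 17.5%)
- 2/47 = 4.3% (0.5% to 14.5%)

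**4. Size of the regrowth ambiguity.** Background describes a series of 90 patients with 28 local recurrences and 6 local failures. Scaled to 47:
- 28/90 × 47 = 14.6
- 6/90 × 47 = 3.1

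If failing locally included salvageable regrowth, about 15 events would be counted instead of about 3. That series had a median follow-up of 60 months, so this shows the order of the gap and does not forecast the two-year result.

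**The case against.** **The analysis is not labelled primary.** It concerns local control, is estimated in both groups, and local control appears again among the time-to-event endpoints. It could be a separate description, with the co-primary endpoint derived in an analysis plan not shown here. The labelling point stands. But this is the only analysis the article gives for local failure at two years, and it is a stated estimator, not a detail left open. An analysis plan that follows it faithfully would carry the mismatch forward.

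**The patient is not lost to safety reporting.** A metastasis-first patient still counts in the two-year distant recurrence rate and in incurable-disease-free survival. This stands. What changes is the attribution to local failure, which is what the co-primary endpoint measures.

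**A reader might infer that the estimate is biased downwards overall and makes watch and wait look safer.** The documents do not support this. The metastasis-first mechanism can only lower the estimate, but counting salvageable regrowth would raise it, possibly by much more. The wording leaves open which reading applies.

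**A reader might set the upper confidence limits above against the 15% in Table 3.** That figure belongs to the early stopping rule. No part of the article compares the final confidence limit with it, so no stated decision turns on that comparison.

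**The effect may be negligible.** At the low end of the assumed ranges it is 0.2 of a patient. This stands as a limit on the size, not on the contradiction.

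**Conclusion.** The point holds as a contradiction between the endpoint definition and the only stated analysis of local failure at two years. It follows from the text alone. Metastasis first with a qualifying local failure later, within two years, is an event under one section and not under the other. That mechanism lowers the estimate by 2.1 points per patient at n = 47. Under assumed D of 5–15% and q of 10–30% the loss is 0.5 to 4.5 points; the true frequency is not given.

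Two limits apply. Local and distant recurrence found together is not clearly lost, because the wording does not settle ties. The net direction of error is not determined while the status of salvageable regrowth is unclear. The sample size is unaffected.

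**What to change.** In Statistical analysis, state that the co-primary estimate is the cumulative incidence of local failure, exactly as defined under Outcomes, to 24 months in the watch and wait arm. Specify that:
- an earlier metastasis or salvaged regrowth neither removes a patient from risk nor counts as an event by itself;
- death without local failure is the only competing event;
- the stopping rule counts the same events;
- the first-event analysis is kept as secondary and labelled so.

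Restricting the endpoint definition to first events would also restore consistency, but it would narrow a safety endpoint.

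The cost is a few sentences and no change in sample size. The downside is small but real: local status must still be recorded after metastasis. Table 1 schedules outcome events at every monitoring visit but does not show that local status is established after metastasis. Patients without such follow-up would be censored at their last local assessment. Because censoring after metastasis may be informative, their number should be reported beside the estimate.
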